### Centre and patient selection

Recruitment of patients will be conducted by investigators at selected study centres in Europe and other regions in which rivaroxaban is approved. Enrolment is planned for approximately 4800 patients with approximately equal numbers in each arm. Patients can be enrolled immediately after a decision about the choice of anticoagulant therapy has been made, but no randomization will be undertaken. Inclusion and exclusion criteria are summarized in Table 2.

**Table 2 T2:** Inclusion and exclusion criteria for XALIA

**Inclusion**	**Exclusion**
● Female or male patients who are ≥18 years of age	● Patients with acute symptomatic PE*
● Diagnosis of acute DVT, objectively confirmed	● Other exclusion criteria are dependent on local product information
● Indication for anticoagulation therapy for at least 12 weeks	
● Patients willing to participate in the study and available for follow-up	

*A parallel symptomatic PE is not an exclusion criterion; however, XALIA will not enrol patients with only PE.

DVT, deep vein thrombosis; PE, pulmonary embolism.

Patients who are ≥18 years old, with a diagnosis of objectively confirmed, acute DVT and an indication to receive anticoagulation for ≥3 months will be included. If anticoagulation is administered for a shorter period than planned, patients will remain in the study.

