### Drug administration

The type, dose and duration of drug therapy are at the sole discretion of the attending physician. Enrolment will only be considered after the treatment decision has been made. Patients who commence treatment with rivaroxaban, or those who initially receive treatment with heparin/fondaparinux within 48 hours of enrolment, can be included in the rivaroxaban cohort. Patients in the standard-of-care cohort are those receiving other recommended pharmacological treatments for VTE according to international guidelines, e.g. initial unfractionated heparin, LMWH or fondaparinux, which may overlap with and be followed by an oral VKA. However, in routine clinical practice many patients for whom rivaroxaban is planned may initially receive parenteral anticoagulants for a period longer than 48 hours before they are switched to rivaroxaban. These patients will be excluded from the main analysis, but the allocation of these patients will be subject to sensitivity tests as follows: 1) they will be analysed separately and 2) they will be allocated to standard of care or rivaroxaban dependent on the distribution of days (after the first 48 hours) in which they actually switched to rivaroxaban; the cut-off points that will be used for these sensitivity analyses will be defined by the quartiles of the distribution of days (after the 48 hours) in which the switch occurs.

Concomitant medications taken prior to or during the study will be documented and include non-steroidal anti-inflammatory drugs, acetylsalicylic acid, clopidogrel, steroids, medications known to interact with the DVT treatment, and medications known to increase or reduce the incidence of DVT (e.g. hormone therapy). Other drugs will be recorded if considered medically relevant by the investigator. Any changes to VTE treatment, including switching or cessation of treatment, will be documented.

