### Statistical analysis

The primary statistical analysis includes a descriptive analysis of the primary and secondary outcomes. The primary outcome variable is the incidence of treatment-emergent adverse events, namely major bleeding and symptomatic recurrent VTE. An adverse event is considered as treatment emergent if it starts on or after the day of the first dose of study medication and ≤2 days after the last dose. All patients who took at least one dose of medication will be included in the safety population. For primary and secondary variables, incidence proportions and incidence rates will be estimated, together with 95% confidence intervals. The accepted range for the 95% confidence intervals is estimated to be between the allocation ratios of 1:3 and 3:1; therefore, at least 25% of patients at each study centre should receive either standard of care or rivaroxaban therapy. To compare the treatment arms, the risk difference and corresponding 95% confidence interval will be calculated, and time-to-event analyses will be conducted.

The potential for allocation bias in open-label, non-randomized studies will be minimized by also presenting a propensity score analysis to control the effect of unbalanced covariates [26,27]. To minimize selection bias, physicians will be asked to document patients consecutively. To decrease the possibility of reporting bias, source data will be verified at approximately 10% of study centres in countries where this is legally possible. A sample size of 4800 patients assumes that 17% of patients will be non-evaluable because of non-overlapping propensity scores or because of withdrawn informed consent forms.

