## Discussion

The demand for real-world data in addition to clinical trial data is increasing. Non-interventional studies are crucial for obtaining a different perspective on the safety and effectiveness of drugs when used in routine clinical practice. Unlike registry data, which is typically analysed retrospectively, studies such as XALIA are designed to assess prospectively defined outcomes of interest thus eliminating potential bias. It is anticipated that XALIA will provide important information on the treatment of DVT in a heterogeneous patient population in a real-world setting. Strict inclusion and exclusion criteria in randomized clinical trials, such as EINSTEIN DVT, may restrict the population in which therapies can be studied, and it is important to show that the findings from clinical trials are applicable to patients treated in routine clinical practice.

One challenge with open-label observational studies is the potential for increased reporting of adverse events with the new drug, otherwise known as the Weber effect [28]. This may be a result of increased patient exposure and higher interest in the drug; however, when physicians become familiar with the drug and its adverse event profile, the rate of reported adverse events usually declines [28]. Therefore, it may be anticipated that this effect will also occur with rivaroxaban, at least during the initial period after its approval for the treatment of VTE.

Findings from XALIA may enable healthcare professionals to gain new insights into the management of patients with DVT, particularly regarding the risks of bleeding and recurrent VTE. Patients are at an immediate and continued risk of recurrence after the first venous thromboembolic event [29], and this risk can be substantial after cessation of anticoagulation [30,31]. Real-world data on recurrence rates will, therefore, be meaningful, particularly in patients who may discontinue anticoagulation. In some cases, the optimal duration of anticoagulation therapy for DVT is unclear; this may be partly owing to challenges in maintaining an appropriate benefit–risk balance because of an increased risk of bleeding or a patient’s intrinsic risk factors [5]. It is hoped that by evaluating the incidence and type of thromboembolic events and bleeding events in XALIA, an accurate representation of the benefit–risk profile of rivaroxaban in routine care will be provided.

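### The plan does not settle whether the adjusted or the unadjusted contrast governs the comparison of two non-randomised cohorts

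*Protocol article*

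**What the plan says.** Under Centre and patient selection: "Patients can be enrolled immediately after a decision about the choice of anticoagulant therapy has been made, but no randomization will be undertaken". Under Drug administration: "The type, dose and duration of drug therapy are at the sole discretion of the attending physician".

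The Statistical analysis section then makes four statements that bear on the comparison:

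- On the primary analysis: "The primary statistical analysis includes a descriptive analysis of the primary and secondary outcomes".
- On the between-arm contrast: "To compare the treatment arms, the risk difference and corresponding 95% confidence interval will be calculated, and time-to-event analyses will be conducted". No adjustment is mentioned here.
- On confounding, in the next paragraph: the potential for allocation bias will be "minimized by also presenting a propensity score analysis to control the effect of unbalanced covariates".
- On size: "A sample size of 4800 patients assumes that 17% of patients will be non-evaluable because of non-overlapping propensity scores", with withdrawn consent as the second reason for the same 17%.

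The section also defines the safety population as every patient with at least one dose. The Abstract and the Conclusions describe the study as comparing rivaroxaban with standard therapy.

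**The concern.** When physicians choose the drug, patients who bleed, recur or die more often for reasons unrelated to it may be concentrated in one cohort. An unadjusted risk difference or survival comparison then mixes the drug effect with that selection. Reporting an adjusted analysis beside it does not take the confounding out of the unadjusted one. The reader still has to know which of the two supports the conclusion.

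The text points both ways. The order of the paragraphs and the word *also* suggest that the adjusted analysis is extra. The evaluability rule behind the sample size suggests that it is central. If the two results disagree, nothing in the section prevents either from being put forward once the data are known. The study is meant to show whether routine-care results are consistent with EINSTEIN DVT, so this choice could decide what is concluded on bleeding, recurrence and death.

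**Working it through.** **1. The plan's own figure.** The article gives no power, effect size or target precision, so 4800 cannot be derived from it. Only the attrition step can be checked:

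- Evaluable patients: 4800 × (1 − 0.17) = 3984, or 1992 per arm at the planned near-equal split.
- Allowance: 4800 − 3984 = 816 patients.
- If the unstated evaluable target was 4000 (an assumption), 1 − 4000/4800 = 16.7%, which rounds to 17%.

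The arithmetic is coherent and is not in dispute.

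**2. What the allowance implies.** Take a treated patient whose propensity score lies outside the overlap region.

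| Comparison | Does this patient contribute? |
|---|---|
| Unadjusted risk difference or time-to-event analysis in the safety population | Yes, fully; one dose suffices |
| Propensity-score comparison restricted to overlap | No |

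Calling such a patient non-evaluable fits only the second row. The section thus sizes the study for one comparison and describes another first. How the 816 divide between non-overlap and withdrawn consent is not stated.

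**3. How large the bias could be.** The documents give no confounder prevalence, strength or direction, so all inputs in this step are assumptions. Suppose there is no true drug effect and one binary risk factor, present in a share pR of rivaroxaban patients and pS of standard-care patients, multiplies event risk by k. Then

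crude RR = (1 + pR(k − 1)) / (1 + pS(k − 1)).

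With pR = 5%:

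| k | pS = 10% | pS = 15% | pS = 20% |
|---|---|---|---|
| 2 | 1.05/1.10 = 0.955 | 1.05/1.15 = 0.913 | 1.05/1.20 = 0.875 |
| 3 | 1.10/1.20 = 0.917 | 1.10/1.30 = 0.846 | 1.10/1.40 = 0.786 |
| 5 | 1.20/1.40 = 0.857 | 1.20/1.60 = 0.750 | 1.20/1.80 = 0.667 |

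If the factor were commoner under rivaroxaban instead, the ratios would invert, from about 1.05 (1/0.955) to 1.50 (1/0.667).

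**4. The same on the risk-difference scale.** Assume a 1% event risk without the factor and 2400 patients per arm.

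- Mild (k = 2, 10% versus 15%): 0.01 × (1.10 − 1.15) = −0.05 percentage points.
- Intermediate (k = 3, 10% versus 20%): 0.01 × (1.20 − 1.40) = −0.20 points.
- Strong (k = 5, 5% versus 20%): 0.01 × (1.20 − 1.80) = −0.60 points. The standard error is √[(0.012 × 0.988 + 0.018 × 0.982)/2400] = 0.35 points, so a two-sided 5% test of the crude difference would reject about 40% of the time with no drug effect.

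For scale, Table 1 gives major bleeding of 0.8% versus 1.2% in EINSTEIN DVT, a difference of −0.4 points. With those rates, the 95% half-width at 2400 per arm is 1.96 × √[(0.008 × 0.992 + 0.012 × 0.988)/2400] = 0.56 points. Mild channelling would be lost in that uncertainty; strong channelling would exceed the reference difference.

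**The case against.** The strongest reply is that the article never calls the risk difference crude, unadjusted or leading. It may simply name the effect measures in one paragraph and the method of adjustment in the next. The propensity analysis is prespecified as the control for allocation bias and is partly built into the sample size. A reader might infer that the plan makes a crude risk difference the lead comparison and reduces the propensity score to a supplement. The text does not support that; it leaves the ranking unsettled.

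A descriptive primary analysis also fits the main objective in the Introduction, which is to evaluate safety by examining the incidence of events. Incidence by cohort needs no adjustment. That stands for the within-cohort figures, but not for the comparison with standard therapy that the Abstract and Conclusions announce.

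It can further be said that a condensed article leaves such matters to the full protocol or analysis plan. That is right for the covariates and the propensity-score method, and their absence is not criticised here. The point is that two statements in the printed section pull against each other.

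The bias figures rest wholly on assumed inputs. The 0.67 needs the extreme corner of the grid, and its closeness to the Table 1 hazard ratios of 0.65 to 0.68 is no evidence of such bias. The principal safety outcome there has a hazard ratio of 0.97.

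Finally, the Discussion describes studies such as this one as "designed to assess prospectively defined outcomes of interest thus eliminating potential bias". A reader might take that as a claim that allocation bias is gone. In context the sentence contrasts prospectively defined outcomes with retrospective registry analysis, and the Statistical analysis section acknowledges allocation bias. The wording is loose, but it governs no analysis.

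**Conclusion.** The concern holds as an inconsistency about which estimate governs. The Statistical analysis section states a between-arm contrast without adjustment and adds the propensity analysis to it, while counting patients as evaluable by a rule that belongs to the propensity analysis. Followed as written, an unadjusted contrast could carry the comparative conclusion.

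The size and direction of any resulting bias are unknown from the documents. A crude risk ratio of about 0.95 to 0.67 under no true effect is a range over assumed confounders (one factor, 5% versus 10–20%, risk multiplied by 2 to 5), not a prediction. Nothing here shows that the sponsor intends to lead with an unadjusted result, and no figure in the sample size statement is wrong.

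**What to change.** In the Statistical analysis section, state that the propensity-score-adjusted comparison in the overlap population, with its 95% confidence interval, is the main between-arm result for each primary outcome. State also that the unadjusted incidences, risk difference and time-to-event results are descriptive and carry no comparative conclusion. The choice should be fixed before outcomes are compared between the arms.

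The change is wording only and needs no new data. The target stays at 4800, since 4800 × 0.83 = 3984 evaluable patients are already allowed for. The price is that the estimate applies to patients in the overlap region and may be somewhat less precise. With the Table 1 major-bleeding rates, going from 2400 to 1992 per arm widens the risk-difference half-width from 0.56 to 0.62 points, before any effect of the adjustment itself on the variance. Tightening the Discussion sentence is optional and not part of this change.

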## Discussion

The demand for real-world data in addition to clinical trial data is increasing. Non-interventional studies are crucial for obtaining a different perspective on the safety and effectiveness of drugs when used in routine clinical practice. Unlike registry data, which is typically analysed retrospectively, studies such as XALIA are designed to assess prospectively defined outcomes of interest thus eliminating potential bias. It is anticipated that XALIA will provide important information on the treatment of DVT in a heterogeneous patient population in a real-world setting. Strict inclusion and exclusion criteria in randomized clinical trials, such as EINSTEIN DVT, may restrict the population in which therapies can be studied, and it is important to show that the findings from clinical trials are applicable to patients treated in routine clinical practice.

One challenge with open-label observational studies is the potential for increased reporting of adverse events with the new drug, otherwise known as the Weber effect [28]. This may be a result of increased patient exposure and higher interest in the drug; however, when physicians become familiar with the drug and its adverse event profile, the rate of reported adverse events usually declines [28]. Therefore, it may be anticipated that this effect will also occur with rivaroxaban, at least during the initial period after its approval for the treatment of VTE.

Findings from XALIA may enable healthcare professionals to gain new insights into the management of patients with DVT, particularly regarding the risks of bleeding and recurrent VTE. Patients are at an immediate and continued risk of recurrence after the first venous thromboembolic event [29], and this risk can be substantial after cessation of anticoagulation [30,31]. Real-world data on recurrence rates will, therefore, be meaningful, particularly in patients who may discontinue anticoagulation. In some cases, the optimal duration of anticoagulation therapy for DVT is unclear; this may be partly owing to challenges in maintaining an appropriate benefit–risk balance because of an increased risk of bleeding or a patient’s intrinsic risk factors [5]. It is hoped that by evaluating the incidence and type of thromboembolic events and bleeding events in XALIA, an accurate representation of the benefit–risk profile of rivaroxaban in routine care will be provided.

The clinical impact of anticoagulant-related bleeding complications is often severe. The case–fatality rate for major bleeding in patients with VTE has been reported to be as high as 11% within the first 3 months [32]. Furthermore, data from the RIETE registry showed that 56% of deaths in patients with VTE who received anticoagulation for 3 months were as a result of bleeding [33]. As mentioned previously, clinical trials are selective in nature, and may underestimate the frequency of bleeding seen in clinical practice. Results from a large community-based trial in the US showed an annual incidence of major bleeding as high as 12–13% in patients with VTE [34]. XALIA will provide valuable information on the incidence of major bleeding events that may occur with rivaroxaban or standard therapy in patients with DVT.

## Conclusions

XALIA is a large, non-interventional study investigating the safety of rivaroxaban compared with standard of care for the treatment of acute DVT in routine clinical practice. Real-world data in a large cohort across multiple countries will be a valuable addition to the results of the EINSTEIN programme. The study was started in June 2012, will complete recruitment in early 2014, and results are expected in 2015.
